## **Statistical Analyses**

Demographic and medical information about the infants will be compared between groups to ensure balance. Then, the primary outcome for analysis will be defined as the between group difference between average BIIP scores in the pre and during echocardiography observations. Mean change scores will be calculated and a 2 Group (Intervention) by Phase (Baseline, Echo) analysis of variance will be used to determine main effects. The confidence interval for the difference in treatment effects will be of primary interest. Any differences in baseline BIIP scores or medical/demographic variables found would be included as co-variables in the analysis. Differences between tn-ECHO times between groups, in the total number of times solutions are administered for each group, and in the overall quality ratings of the tn-ECHOs will be compared using paired t tests.

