## Purpose & Objective

Primary Objective: To compare the effect of a 25% glucose solution given via a soother with or without facilitated tucking with a similarly administered water placebo (control condition) on infant stress responses during and immediately after a tn-ECHO.

Secondary Objectives: To compare the performance time of a standard-defined tn-ECHO, the total number of times solutions are given, and the overall quality of the tn-ECHOs between treatment groups.

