## **Hypotheses**

1. When given 25% glucose, soother and/or facilitated tucking during functional echocardiography, infants will show the lower behavioral stress scores than infants in the control groups.
2. When given 25% glucose, soother and/or facilitated tucking during functional echocardiography, the time taken by neonatologists to conduct the procedure will be less than for infants in the control groups.
3. The number of repeated application of the solution will be lower in the infants receiving the glucose solution.
4. The quality ratings of the tn-ECHOS will be higher in the group of infants who receive sucrose+soother/and or facilitated tucking).

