## **Study Design**

Fatorial 4-arm, randomized double blind controlled study.

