## **Methods**

Parents will be asked for written informed consent prior to randomization. It is not standard of practice to obtain parental consent for procedures like echocardiography that are clinically indicated; therefore, the consent will be purely for research purposes.

One hundred and four infants will be randomized to one of four intervention groups (Grp 1: glucose + soother; Grp 2 glucose + soother + facilitated tucking; Grp 3: water + soother; Grp 4: water + soother+facilitated tucking) which will take place during a single tn-ECHO examination, at the discession and after consultation with the medical team.

Randomization to each group will be determined by generating randomly permuted sequential blocks of four and six allocation numbers. The Clinical Services Research Unit will initiate the randomization process and provide the information regarding group allocation that will guide the intervention. Access to the randomization list will be through a web-based system that will enable online interactive checking of the inclusion/exclusion criteria before authorizing random allocation. This system is very reliable with 24-hour on-line support; as part of the data management services, a person will be available by phone during working hours at C&W to provide back-up for the system for unanticipated events. Randomization and preparation of the solutions will then be done by the pharmacist on site who will provide the solutions in unmarked syringes containing 5ml of either water or 25% glucose.

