### **Sample Size Estimate**

In infant studies where self-report is not possible, a 2 point difference in pain scores has been considered clinically significant (10% reduction). Twenty five infants per group (100 total) will yield 80% power for a difference corresponding to the anticipated difference of 2 points on the

BIIP scale between treatment groups. Allowing for potential attrition of 10% and the need for including one or two co-variables in the analysis (e.g. differences in behavioral state at baseline), we may need to recruit up to 115 infants.

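### The primary analysis is a two-group model for a four-arm factorial, it contradicts itself on which term carries the treatment effect, and its covariates are picked from observed differences

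*Protocol*

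**What the plan says.** - **Design.** Study Design describes a "Fatorial 4-arm, randomized double blind controlled study". Methods adds that "One hundred and four infants will be randomized to one of four intervention groups": glucose + soother (Grp 1), glucose + soother + tucking (Grp 2), water + soother (Grp 3) and water + soother + tucking (Grp 4). This is a 2 x 2 layout with the soother in every cell.
- **Objective.** Purpose & Objective sets out the primary aim: "To compare the effect of a 25% glucose solution given via a soother with or without facilitated tucking with a similarly administered water placebo". Water is labelled there as the control condition.
- **Hypothesis 1.** For glucose, soother and/or tucking, "infants will show the lower behavioral stress scores than infants in the control groups".
- **Primary analysis.** Statistical Analyses defines the outcome as the between-group difference in BIIP from before to during the echo. It has mean change scores calculated and makes the confidence interval for the difference in treatment effects the quantity of main interest. It also says that "a 2 Group (Intervention) by Phase (Baseline, Echo) analysis of variance will be used to determine main effects".
- **Covariates.** "Any differences in baseline BIIP scores or medical/demographic variables found would be included as co-variables in the analysis".

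**The concern.** There are three separate faults in one short paragraph.

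1. **The model does not fit the design.** It has two groups and two phases. Tucking, a randomised factor, does not appear, and neither does the glucose-by-tucking term. Which arms make up the two groups is not stated, and the objective and Hypothesis 1 can be read as placing Grp 4 on opposite sides. A quarter of the infants could therefore be counted as control or as intervention, and the protocol would allow that choice to be made after the data are seen.
2. **The paragraph names two different targets.** The outcome definition, the change scores and the confidence interval point to the Group-by-Phase contrast. Reading the ANOVA on main effects points elsewhere: the Group term averages in a baseline taken before any intervention, and the Phase term does not compare treatments.
3. **Covariates are selected from the data.** Whether the primary estimate is adjusted, and for what, depends on chance imbalance. Baseline BIIP is collected in every infant but becomes a covariate only if the groups happen to differ on it.

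**Working it through.** **The plan's own figure.** Sample Size Estimate gives 25 per group and 80% power for an "anticipated difference of 2 points on the" BIIP scale. It states no SD, alpha or sidedness. With two-sided alpha 0.05 (assumed) and the normal approximation, the implied SD is 2 / [(1.960 + 0.842) x √(2/25)] = 2.52. That is close to the heel-lance SD of 2.6 in Outcome Measures, at which 25 v 25 gives 78% (76% by noncentral t). The figure is plausible as a pairwise two-sided calculation but cannot be confirmed.

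**What the choice of two groups does.** Let g be the glucose effect, t the tucking effect and i their interaction, with equal arms and Grp 3 as reference.
- Glucose v water (Grps 1+2 v 3+4; 52 v 52 of 104): [g + (g + t + i)]/2 − [0 + t]/2 = g + i/2.
- Any active component v neither (Grps 1+2+4 v 3; 78 v 26): [g + (g + t + i) + t]/3 = (2g + 2t + i)/3.

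If only glucose works (g = 2, t = i = 0), these give 2.00 and 1.33 points. If only tucking works (t = 2, g = i = 0), they give 0 and 1.33. The two groupings answer different questions. Taken literally, Hypothesis 1 also lists the soother, which all four arms receive, and that would leave no control arm.

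**Which term carries the effect.** Procedures has baseline BIIP scored before tucking or solution starts, so the expected group difference at baseline is 0. Let it be d during the echo.
- Group main effect: (0 + d)/2 = d/2, so 1 point when d = 2.
- Group-by-Phase contrast (difference in change scores): d − 0 = d, so 2 points.

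A simulation of 20,000 trials at each of correlations 0 and 0.5 (SD 2.524, 25 v 25) returned 1.00 and 2.00.

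**Power.** Inputs are SD 2.6 in both phases, baseline-to-echo correlation r (not in the protocol, so shown as a range) and two-sided alpha 0.05, by noncentral t. The per-infant SDs are:
- mean of two phases: SD x √((1 + r)/2); at r = 0.3, 2.10
- change score: SD x √(2(1 − r)); at r = 0.3, 3.08
- baseline-adjusted (ANCOVA): SD x √(1 − r²); at r = 0.3, 2.48

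Each standard error is that SD x √(2/n). The effect is 1 point for the first and 2 points for the others.

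| r | n per side | Group main effect | Change score | ANCOVA |
|---|---|---|---|---|
| 0 | 25 | 47% | 47% | 76% |
| 0.3 | 25 | 38% | 62% | 80% |
| 0.7 | 25 | 30% | 93% | 96% |
| 0 | 50 | 77% | 77% | 97% |
| 0.3 | 50 | 66% | 90% | 98% |
| 0.7 | 50 | 54% | >99% | >99% |

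With the other SD in Outcome Measures, 0.5 for diaper change, the main-effect standard error at 25 v 25 and r = 0.3 is 0.403 x √(2/25) = 0.114. One point is then almost nine standard errors, and power is near 100% for every analysis.

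**Covariate rule.** The ratio of ANCOVA to change-score variance is (1 − r²)/[2(1 − r)] = (1 + r)/2, or 0.65 at r = 0.3. Using baseline BIIP as a covariate only when a difference is found means switching between two estimators of different precision according to observed imbalance. Sample Size Estimate allows for one or two covariates. Statistical Analyses sets no limit and no criterion for a difference.

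**The case against.** **The paragraph already contains the right estimand.** This is the strongest reply, and it stands in part. The outcome definition, the change scores and the confidence interval all recover the full effect, and main effects may have been meant loosely, as the factorial main effects. A reader might infer that the primary test targets half the treatment effect. The text does not establish that; it follows only from a literal reading of one clause. What stands is that the clause conflicts with the sentences around it, and the only factors it names are Group and Phase.

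**The power loss depends on the inputs.** A reader might also infer that most of the planned power is lost. The objective suggests glucose v water, about 50 v 50, where even the literal main effect keeps about 66% at r = 0.3. The 38% belongs to a 25 v 25 comparison, which a two-group analysis of all four arms would not make. With SD 0.5 there is no loss at all. An echo is arguably nearer to a non-skin-breaking procedure than to a heel lance, and an echo score averaged over observations may vary less than a single baseline score.

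**Grp 4 is partly settled.** The objective makes water the control, and Hypothesis 1 refers to control groups in the plural, which fits both water arms. The and/or wording still allows the other reading.

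**Covariates.** It is tempting to attach a probability that some covariate is selected by chance. The protocol gives neither the number of variables nor a threshold, and variables such as birth weight and gestational age are not independent, so no figure is supported. Change scores already use baseline BIIP in every infant; ANCOVA adds precision and does not remove a bias.

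**A SAP may give the detail.** It may. But the protocol has named a primary model, and a SAP that followed it could not also analyse the factorial.

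**Conclusion.** The point holds as a mismatch and an inconsistency in the primary analysis. Followed as written, the model leaves tucking and the glucose-by-tucking interaction unanalysed, does not say where Grp 4 belongs, and lets chance imbalance determine the covariates. None of this depends on an assumed number.

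The halving is conditional. It applies only if the Group main effect is taken as the test, and its cost in power rests on SD 2.6 in both phases, an assumed correlation and two-sided alpha 0.05. On those terms, over correlations 0 to 0.7, main-effect power is 77% to 54% at 50 v 50 and 47% to 30% at 25 v 25. With SD 0.5 the cost vanishes, though the estimate would still be half the effect. The documents do not support saying that the trial will test half its effect or lose most of its power. They do support saying that two incompatible readings of the primary result are open and that one must be removed.

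**What to change.** - **Model.** State the primary model as mean BIIP during the echo = glucose + tucking + glucose x tucking + baseline BIIP, and name the observations that make up the during-echo mean.
- **Contrasts.** Make glucose v water, averaged over tucking, the primary contrast with its 95% CI. Follow it with tucking v no tucking, and report the interaction with its interval.
- **Covariates.** Fix baseline BIIP in advance and delete the rule that adds any differences found. The gestational-age band used for solution volume may be added, also in advance; its limits are written differently in two places in Procedures and must be reconciled first.
- **Main effects.** Delete the reading of the Group x Phase ANOVA on main effects.
- **Hypothesis 1.** Reword it so that Grp 4 has one role and the soother, given in all arms, is not presented as a tested component.

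The cost is wording only: no new data, no change to randomisation and no extra infants. One small downside is that the marginal contrasts are interpretable only if the glucose-by-tucking interaction is not large, which is why it should be reported beside them.

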## **Procedures**

All testing will take place in the NICU and Intermediate Nursery at C&W. As in our previous studies, five minutes before, during and five minutes after the tn-ECHO procedure, a close up image of each infant's face and upper extremities are videotaped. The digital, color camera is set up using a tripod. Using a foot pedal attached to the camera, recordings are synchronized to mark events. These tapes will be used to provide blinded behavioral coding of our primary outcome measure in conjunction with our bedside scoring described below.

For all groups, each infant will remain in his/her incubator/cot, positioned with rolls around the body to promote a flexed position. Every attempt will be made to have the procedure scheduled one hour post feed, if the infant is feeding. After a 20 minute rest period, five minutes before the contact of the physician to conduct the examination, an attending physician who is not conducting the tn-ECHO will assess the infant's baseline stress levels over a 30 second period using the Behavioral Indicators of Infant Pain (BIIP). BIIP score will then be measured 2 min after first administration of the solution (at time of starting of the tn-ECHO), then halfway through the assessment (as defined per echocardiographical images obtained, after completion of the right ventricular long axis view with RVO), and finally immediately after the last contact of the physician.

With respect to the glucose/water administration, two minutes before the first contact by the physician performing the tn-ECHO, each infant will be given either 0.5ml of 25% glucose (26-31 weeks gestational age group) or 1.0 ml of 25% glucose (32-42 weeks gestational age group). The solution will be applied to the anterior portion of the tongue followed by insertion of a soother. The soother will be held in the infant's mouth to ensure that continuous contact is maintained throughout the testing period. During the course of the assessment (estimated about 20 min), this application can be repeated if necessary (if the infant's movements interfere with the quality of picture obtained) to a maximum of four times, adding up to max 2ml of 25% glucose in the 27-31 weeks gestational age group or 4ml of 25% glucose in the 32-40 weeks gestational age group. During each tn-ECHO, infants have additional handling only if it is required to maintain physiological stability. Pharmaceutical interventions are an exclusion criterion for the study.

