### *Secondary Outcome Measures*

The secondary outcome measures will be the time to complete a standard tn-ECHO assessment, which will be defined when ultrasound images have been acquired for all four cardiac views (see appendix), the total number of times solutions are given to the infants, and the quality of images.

Quality of tn-ECHO images: The quality of tn-ECHO images will be rated by 2 neonatologists/cardiologists blind to the treatment groups and to any clinical information about each patient. A scale for rating the overall quality was designed (attached) in consultation with the Cardiology Department. Before the start of the study, a pilot of 10 tn-ECHOs will be rated to ensure starting inter-rater reliability is achieved (agreement > 85%). Then, inter-rater reliability will be checked between raters after ½ the study patients are enrolled. Inter-rater reliability will be assessed using the Bland and Altman approach which analyzes the differences in scores between two coders over the pair-wise mean of the two coders.

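### The secondary outcomes are to be compared between independently randomised infants with paired t tests, although the design contains no pairs

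*Protocol*

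**What the plan says.** The protocol's Statistical Analyses section covers all three secondary outcomes in one sentence. It begins "Differences between tn-ECHO times between groups, in the total number of times solutions are administered for each group" and ends "and in the overall quality ratings of the tn-ECHOs will be compared using paired t tests". The contrast is between groups and the named test is paired.

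The design sections describe something else:

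- Study Design: "Fatorial 4-arm, randomized double blind controlled study".
- Methods: "One hundred and four infants will be randomized to one of four intervention groups", with an intervention "which will take place during a single tn-ECHO examination".
- Methods, on allocation: "Randomization to each group will be determined by generating randomly permuted sequential blocks of four and six allocation numbers". Matching of infants is not mentioned.
- Secondary Outcome Measures: "The secondary outcome measures will be the time to complete a standard tn-ECHO assessment", together with the number of administrations and the image quality.
- Procedures: repeat applications are limited "to a maximum of four times", so the administration count is a small, bounded integer.

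**The concern.** A paired t test analyses differences within natural pairs: the same infant twice, or infants matched by design. Here the infants in different arms are unrelated. The protocol names a specific test that cannot be carried out on the data it describes unless someone decides which infant is set against which.

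That sentence is the protocol's only stated analysis for hypotheses 2, 3 and 4 (shorter scans, fewer applications, better images). What is at stake is whether those results are uniquely defined in advance or depend on a choice made at analysis.

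**Working it through.** **1. Is there any source of pairs?** The candidates in the protocol are these:

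- Crossover or repeat scans: none. Each infant has a single examination.
- Matching at randomisation: none. Permuted blocks of four and six balance numbers over time but do not form pairs. A block of six cannot be split equally over four arms (6 / 4 = 1.5).
- Repeated measurement: only the BIIP is scored at several phases within an infant. Scan time, administration count and image quality each describe the whole examination.
- Two raters of image quality: pairing them would test agreement between raters, not the difference between treatment groups.

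No reading supplies pairs.

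**2. What does an invented pairing do?** Take two arms of n = 25, the figure per group in Sample Size Estimate. (The 104 infants in Methods would give 104 / 4 = 26.) For values a and b with sample variances s_a² and s_b²:

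- Independent test: SE = √((s_a² + s_b²) / n), df = 2n − 2 = 48, two-sided 5% critical t = 2.011.
- Paired test: SE = √((s_a² + s_b² − 2s_ab) / n), df = n − 1 = 24, critical t = 2.064.

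With equal arms the mean difference is the same under every pairing. The covariance s_ab is not: it is pure noise from the arbitrary order, and it moves the standard error, the p-value and the interval. The loss of degrees of freedom alone widens the interval by only 2.064 / 2.011 = 1.026, or about 2.6%. With unequal arms the surplus infants have no partner and are dropped, so the estimate itself then depends on the pairing. Unequal arms are likely, given the 10% attrition allowed for in Sample Size Estimate.

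**3. Error rates when the pairing ignores outcomes.** Simulation with 40,000 replicates, normal data, 25 per arm, two-sided alpha 0.05 (the protocol states no alpha):

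| | Independent | Arbitrarily paired |
|---|---|---|
| Rejection under no effect | 4.98% | 4.88% |
| Power at a difference of 0.81 SD | 79.8% | 78.3% |

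The difference of 0.81 SD is the one that 25 per group detects with 80% power. The protocol gives no power figure for the secondary outcomes to reproduce.

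**4. How far can the result move on one data set?** Data for 25 v 25 were scaled so that the independent test gives a fixed p-value, and one arm was then repeatedly reshuffled against the other:

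| Independent p | Share of pairings with paired p < 0.05 |
|---|---|
| 0.001 | 100% |
| 0.01 | about 100% |
| 0.05 | about 40% |
| 0.20 | 0.1% to 0.2% |

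At an independent p of 0.05, the central 95% of paired p-values ran from about 0.017 to 0.105. The pairing decides the conclusion mainly near the threshold.

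**The case against.** The strongest defence is that this is probably a slip for unpaired, that any analyst would notice it once the arms turned out unequal, and that a pairing fixed without sight of the outcomes does little harm on average. The last part stands, as the error rates show. The first two do not remove the point: the protocol text is explicit, nothing else in it corrects the sentence, and a fixed plan should not depend on the analyst departing from it.

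Three stronger readings are tempting, and the protocol does not support them.

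- *Hypotheses 2 to 4 are left with no valid test.* Outcome-blind pairing keeps the level near 5%. The fault is that the test does not apply and is not uniquely defined, not that its error rate is inflated.
- *Four arms in themselves rule out a t test.* A factorial main effect is a two-group contrast, about 52 v 52 with 104 infants, and an independent two-sample test can handle it. The sentence simply does not name such a contrast.
- *The wording commits the trial to a large family of pairwise tests with a high false-positive rate.* No section plans all pairwise comparisons of the four arms. Contrasts that share arms are also correlated, so a calculation that treats them as independent overstates the risk. Multiplicity for secondary outcomes is a separate matter that may properly be left to the SAP.

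**Conclusion.** The point holds in a narrow form. The test named for all three secondary outcomes does not match a parallel-group design with one value per infant. Average type I error and power are barely affected. What is lost is a unique, prespecified answer: the p-value and interval depend on an arbitrary pairing, infants are discarded when arms differ in size, and a 25 v 25 contrast keeps 24 of its 48 degrees of freedom. A conclusion would change mainly for results near p = 0.05.

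The figures assume normal data, 25 infants per arm and a two-sided 5% level. The finding that no pairs exist rests on none of these. Only secondary outcomes are affected. Data collection, the sample size and the primary BIIP analysis are not. This should be fixed, but it does not threaten the trial's main result.

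**What to change.** In Statistical Analyses, replace the paired t tests with independent-groups analyses that follow the 2x2 design. For example:

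- **Scan time:** a two-way linear model with glucose and tucking as factors. Report the glucose and tucking main effects with 95% confidence intervals. If the interaction is included, obtain them as marginal contrasts (effect coding). Under ordinary 0/1 coding those coefficients are simple effects at one level of the other factor.
- **Number of administrations:** a count, ordinal or rank-based method, because the count is capped.
- **Image quality:** an ordinal or rank-based method if the rating scale is ordinal. The scale is an attachment that is not in the text at hand, so this choice depends on its form.

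Further modelling detail can be left to the SAP. The cost is one sentence, with no extra infants and no extra data. All infants with an observed outcome can then be used: with 100 infants, the four-cell model has 100 − 4 = 96 error degrees of freedom.
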